## Methods

### Study objectives

The primary objective of this study is to evaluate the effectiveness and impact of RASP on high-cost health services utilization (e.g. ED visits, mobile crisis visits and inpatient mental health utilization). To achieve this objective, we will conduct a within-subject comparison by analyzing health services utilization data from patients attending the RASP program one year pre- and post-assessment. Additionally, a between-subject comparison will be made using historical data from a control population consisting of patients referred by a PHP to see a mental health clinician before RASP implementation. Another primary objective is to assess qualitative data from healthcare partners' perceptions related to the impact of the RASP on access to community mental health care for patients and support for primary care providers, as well as to determine patient experiences and satisfaction with the program.

The secondary objectives of this study are to i) identify the sociodemographic characteristics of the population assisted by the RASP, ii) evaluate the prevalence and correlates of the various psychological conditions of the assisted population, iii) assess recovery, well-being, and risk measures in the assisted population at the program entry, and iv) compare health services utilization in the subset of patients who opt to participate in the Text4Support RCT with those who do not.

The study seeks to address the following research questions:A.Effectiveness and Impact on Health Services Utilization of the RASP:Did RASP increase the volume of patients referred by PHP? Measured by the number of patients referred by a PHP for a psychiatrist consultation before and after RASP implementation.Did RASP increase the proportion of patients triaged by Central Intake services who had direct access to psychiatric consultations? Measured by the proportion of referrals received by central intake that were booked directly for psychiatry consultation, before and after RASP implementation.Did RASP reduce wait times for access to psychiatrists in the publicly funded MHAP? Measured by the number in calendar days waiting from date referral was received by Central Intake to date patient is scheduled for a psychiatric consultation before and after RASP implementation.Did RASP improve efficiency of the Community Mental Health Programs (CMHP) to address the mental health needs of patients with complex mental health needs? Measured by wait-times for assess to psychiatrists within the CMHP following a referral by a mental health clinician before and after RASP implementation.Did RASP reduce the volume of patients referred by PHP to the ED for a psychiatric consultation? Measured by the number of patients referred by a PHP for a psychiatrist consultation at the ED before and after RASP implementation.Did RASP reduce ED visits, mobile crisis visits, and inpatient mental health services utilization? Measured by the number of mental health and addictions (MHA)-specific ED visits, number of mobile crisis visits, number of MHA-specific hospital admissions, and number in calendar days in LOS for Central Zone patients, before and after RASP implementation.Did patients who attended the RASP and opted to participate in the Text4Support RCT differ in their health services utilization compared to patients who opted not to participate in the Text4Support RCT? Measured by the number of MHA-specific ED visits, number of mobile crises calls, number of MHA-specific hospital admissions, and LOS in calendar days, one-year post-RASP assessment.What are the costs and benefits to Nova Scotia Health from having a RASP for mental health? Measured by the net cost savings associated with RASP considering costs associated with the program and costs saved from avoided high-cost health services utilization (ED visits, mobile crisis visits, and inpatient treatments).B.Perspectives and Experiences of Healthcare Partners and PatientsWhat are healthcare partners' perceptions related to the impact of the RASP on access to community mental health care for patients and support for primary care providers? Measured by qualitative data from key informant interviews with program directors, psychiatrists, primary healthcare providers, MHA service leaders, and representatives from community organizations.What are the patients' perceptions related to their overall experience and satisfaction with the service received? Measured by quantitative and qualitative data from the RASP's satisfaction survey and qualitative data from focus group sessions with a sub-group of the assisted population.C.Population Characteristics and Mental Health MeasuresWhat proportion of patients seen at the RASP continued their treatment with PHP? Measured by the number of patients fully discharged back into the care of their primary healthcare provider with treatment recommendations (chart review data).What proportion of patients seen at the RASP were referred to a community mental health program? Measured by the number of patients referred to a community mental health program by RASP psychiatrists (chart review data).What proportion of patients seen at RASP needed additional psychiatric evaluation at the RASP? Measured by the number of re-referrals to RASP by a PHP.What are the sociodemographic characteristics of the assisted population at program entry? Measured by the frequency and percentages of the sociodemographic characteristics (e.g. age, sex of birth, gender, ethnicity, employment status, source of income, income range, relationship status, family support, housing status, education, provincial zone) (chart review data).What is the status of patients’ recovery and health quality index, and the prevalence of likely major depressive disorder (MDD), likely generalized anxiety disorder (GAD), low resilience, childhood trauma, substance use, and suicide risk at program entry? Measured by patient-completed validated scales scores (chart review data).What is the prevalence of patients' diagnoses made by RASP psychiatrists at program entry? Measured by the frequency and percentages of each psychiatry diagnosis after psychiatry assessment (chart review data).What are the risk factors for ED presentation for mental health concerns and inpatient psychiatric treatments? Measured by Odds Ratios using logistic regression models with sociodemographic and clinical data from the assisted population one year before and after RASP assessment date.

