## Background

### Mental health and the burden on health services utilization and health outcomes

Emergency psychiatric care, unplanned hospital admissions and inpatient health care are the costliest forms of mental health care [1]. The frequency of Emergency Department (ED) presentations with mental health concerns and length of psychiatric hospitalizations can have significant physical, psychological, and financial consequences for patients and their families and affect the infrastructural, human, and economic well-being of healthcare systems [2, 3]. This is especially true in the era of the COVID-19 pandemic when already limited services have been further stretched by growing hospital admissions, ED presentations and an increase in extended stays [4–6]. The World Health Organization reported in October 2020 that the pandemic had disrupted or halted critical mental health services in 93% of countries worldwide [7]. Consequently, the increased demand for mental health support has renewed the interest in seeking out solutions to mitigate avoidable hospital readmissions and ED visits, as well as to lower lengths of stay (LOS) in acute care facilities [8].

People with psychiatric disorders have the highest early readmission rates among all hospitalized patients [9–11]. Early readmission is defined as readmission within 30 days of previous discharge [9]. Although deinstitutionalization of care and transition to community-based mental health care has been an approach of focus for decades [12, 13], early hospital readmission rates remain high. In Nova Scotia, the 30-day re-admission rate for inpatient mental health treatment was 10.14% for the 2021/2022 fiscal year. The unmet need for psychological treatment and the limited human resources to address this gap is a major cause of readmission in acute psychiatry units [9]. The readmission rate is a prevalent indicator used for quality assessment of care and a focus of interest for health sector policymakers [14, 15]. In psychiatry, readmission rates are usually commensurate with relapse or complications following an inpatient stay. While it may reflect premature discharge from inpatient psychiatric units, it may also relate to the lack of coordination of post-discharge healthcare services [16, 17].

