### Participants and data collection

All RASP patients receive a consent form as part of their intake process, allowing access to their health services utilization records. Only those who sign the consent form will be part of the study. While consent is obtained during the initial assessment for ongoing patient recruitment, data collection is scheduled to commence after the program's first year, in April 2024. Service utilization data will extracted from provincial information systems retrospectively and prospectively at 2-time points: one year pre- and one-year post-assessment date at RASP. In addition, sociodemographic and mental health assessment information, including results from patient-completed validated scales and psychiatry diagnosis, and patient satisfaction will be extracted from routine paper-based initial screening forms. Patient satisfaction quantitative data will be extracted from RASP's patient satisfaction survey, available in a paper-based format and completed immediately after the assessment or REDCap online survey link sent via text message to all patients attending the service just after the assessment appointment.

The control group for the cohort study will comprise patients referred to the MHAP Central Intake Services by a PHP before RASP implementation. The periods for inclusion in the control group will be May 2017 to May 2019 (pre-COVID) and May 2020 to May 2022 (during COVID). By examining the data from these two time points (pre-COVID and during COVID) and comparing them with each other and with data during the RASP implementation period, we will be able to evaluate the impact of the pandemic on health services utilization as well as the impact of RASP implementation in comparison with both the pre-pandemic and during the pandemic periods. Ethics approval for exemption from requiring informed consent for all control group patients has been granted by the Research Ethics Board at Nova Scotia Health (REB file #1028254), allowing control group patients' sociodemographic and health services utilization information from provincial administrative databases to be accessed by the investigators.

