For the qualitative component of the study, expected to take place after a year of RASP implementation, in April 2024, a sub-sample from the overall pool of the intervention population (RASP patients) will be invited by a research team member to participate in a focus group session. The inclusion criteria to participate in the qualitative sub-study are to provide consent and be available to attend a 1-hour focus group session, which will be audio-recorded. The focus group script will be developed by investigators, reviewed by healthcare partners, piloted with patients and adjusted as needed, before being used in the focus groups. A trained research team member will conduct the encounters, which may happen in person or via Zoom. The sample size for the qualitative component of the study cannot be predetermined because data saturation needs to be reached. Data analysis ends when no new themes and subthemes emerge across all analysts. However, based on what the literature suggests [37], we anticipate that 25-30 participants may be sufficient for this mixed-methods study. Participants will receive compensation for their time spent participating in the qualitative sub-study activities.

Healthcare partners involved with RASP will be also actively engaged in the qualitative evaluation of the program. Trained members of the research team will conduct individual key informant interviews, either virtually or in person, with program directors, psychiatrists, primary healthcare providers, MHA service leaders, and representatives from community organizations. These interviews aim to gather in-depth information about healthcare partners' experiences and opinions regarding the program, allowing for a comprehensive understanding of their perspectives.

Finally, a sub-population of RASP patients who opted to participate in the Text4Support RCT will also have their one-year pre- and post-RASP attendance health services utilization data collected and compared to patients who chose not to participate in the optional Text4Support RCT. RASP was launched in April 2023, with data collection ongoing. Table S2 demonstrates in detail the variables, sources and data collection time points.

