### Outcome measures

Primary outcome measures will include the mean differences in the frequency/duration/related costs of high-cost mental health services utilization (i.e., volume and proportion of mobile crisis visits, ED visits, hospital admissions and readmissions and associated LOS for each admission) between one year pre- and post-assessment date for same patients at RASP (within-subject comparison) and between the IG (RASP) and CG (historical data) (between-subjects comparison). Other primary outcome measures will be the mean difference in the number and proportion of total referrals booked directly for a psychiatrist and the number of calendar days for access to psychiatrists, also compared to the control group.

Secondary outcome measures include the mean difference in the frequency/duration/related costs of high-cost health services utilization one year post for patients who access the RASP and participate in the Text4Support RCT (to receive either daily supportive text messages or a single text message with a link to e-mental health resources) and patients accessing RASP but who do not participate in the Text4Support RCT. Other secondary outcome measures include a descriptive summary of the sociodemographic and clinical characteristics of the assisted population, the mean scores on the Patient Health Questionnaire 9 (PHQ-9) [38], Generalized Anxiety Disorder 7 (GAD-7) [39], World Health Organization 5 (WHO 5 Well-Being Index) [40], Brief Resilience Scale (BRS) [41], Recovery Assessment Scale (RAS) [42], Adverse Childhood Experience (ACE questionnaire) [43], Brief Substance use Craving Scale (BSCS) [44], and the Columbia-suicide severity rating scale (C-SSRS) [45], as well as the prevalence of likely MDD, GAD and low resilience. Patient overall impressions (i.e. barriers to accessing RASP, satisfaction level, likely recommend the service to others, etc.) and impressions on the experience (i.e. feelings of welcomeness, respect, enough time to talk, the problem addressed, and understanding of treatment) are part of the patient satisfaction quantitative evaluation. An in-depth evaluation of healthcare partner impressions and patient satisfaction will be obtained through qualitative key informant interviews until saturation is reached and no new themes and subthemes emerge.

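### The access measures are before/after or historical-control contrasts with no pre-launch trend, so secular change is not separated from a RASP effect

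*Protocol article*

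**What the plan says.** Research question A in the Study objectives section of the protocol article asks, in causal terms, whether RASP increased PHP referral volume, increased direct access to psychiatric consultation and reduced waits. Each is given a two-period measure:

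- Referral volume: "Measured by the number of patients referred by a PHP for a psychiatrist consultation before and after RASP implementation".
- Direct booking: "Measured by the proportion of referrals received by central intake that were booked directly for psychiatry consultation, before and after RASP implementation".
- Waits: calendar days from receipt of the referral at Central Intake to the "date patient is scheduled for a psychiatric consultation before and after RASP implementation".

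The Outcome measures section gives two of these primary status: "Other primary outcome measures will be the mean difference in the number and proportion of total referrals booked directly for a psychiatrist", together with calendar days to psychiatrist access, both compared with the control group. Referral volume is a research question and is not listed there as a primary outcome.

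The Participants and data collection section fixes the historical windows: "The periods for inclusion in the control group will be May 2017 to May 2019 (pre-COVID) and May 2020 to May 2022 (during COVID". It says the two windows will be compared with each other and with the RASP period. It also gives the start of the program: "RASP was launched in April 2023, with data collection ongoing". The Quantitative analysis section adds propensity score matching and regression adjusting for the periods before, during and after the pandemic. The ANCOVA described there uses a patient's utilization in the preceding year as its covariate.

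**The concern.** A difference between two periods equals the program effect only if nothing else would have moved the measure between them. The Background gives reason to doubt that: "the increased demand for mental health support has renewed the interest in seeking out solutions", said of the pandemic period before RASP existed. If referrals were already rising, a later period would show more of them whether or not RASP had been launched.

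Booking practice and waits can drift for their own reasons too, including a pandemic backlog that builds and then clears. The plan states no pre-launch trend, no segmented model and no concurrent comparator for these measures. Two of the three are primary, and the questions attribute any change to RASP. At stake is whether the access findings can be credited to the program at all.

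**Working it through.** The plan gives no expected effect or calculation for the access measures, so there is no figure of its own to reproduce. The sample size of 525 per group concerns utilization and has no bearing here.

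**Step 1. Distance between the periods.** Inputs: control windows May 2017 to May 2019 and May 2020 to May 2022; launch in April 2023; a 24-month data collection period (Sample size considerations). I assume that the 24 months run from launch. The midpoints are then May 2018, May 2021 and April 2024.

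- May 2021 to April 2024: 35 months = 2.917 years.
- May 2018 to April 2024: 71 months = 5.917 years.

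**Step 2. Apparent change in referral volume with no RASP effect.** With steady yearly growth g, the spurious rise is (1 + g)^gap − 1. For g = 3%: 1.03^2.917 − 1 = 9.0% and 1.03^5.917 − 1 = 19.1%. The growth rates are assumptions, because the documents give none:

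| Assumed growth per year | Against May 2020–May 2022 | Against May 2017–May 2019 |
|---|---|---|
| 1% | +2.9% | +6.1% |
| 3% | +9.0% | +19.1% |
| 5% | +15.3% | +33.5% |
| 10% | +32.0% | +75.8% |

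**Step 3. Does the stated period adjustment help?** Code each window by intercept, RASP, during-COVID and post-COVID:

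| Window | Intercept | RASP | During | Post |
|---|---|---|---|---|
| May 2017–May 2019 | 1 | 0 | 0 | 0 |
| May 2020–May 2022 | 1 | 0 | 1 | 0 |
| RASP period | 1 | 1 | 0 | 1 |

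The RASP and post-COVID columns are identical, so the matrix has rank 3 of 4 and the two effects cannot be told apart. Comparing the two historical windows with each other may reveal drift, but no term carries that drift forward to the RASP period. Propensity matching balances patients and cannot be applied to an aggregate count. It can be applied to waits and booking status, which exist per patient or referral, but matching on patient characteristics does not remove calendar time.

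**Step 4. Simulation with no RASP effect.** Monthly counts from May 2017 to March 2025, with the May 2020 to May 2022 block against the RASP block, tested at 5%:

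- 100 referrals a month, Poisson, 1000 runs. At 3% growth the block ratio is 1.09 and significant in 89% of runs; segmented regression gives a level ratio of 1.00, significant in 4.8%. At 5% growth the block ratio is 1.15 and significant in 100%; segmented regression gives 1.00 and 5.6%.
- 200 referrals a month with extra-Poisson variance of 0.02 or 0.005, 400 runs per cell. The block contrast is significant in 27–57%, 49–86% and 90–100% of runs at 2%, 3% and 5% growth; segmented regression in 4–8%.
- 200 referrals a month, a 10% pandemic dip and a correctly timed COVID term in the model. The segmented step ratio is 0.997–1.006 and significant in 4–8%. At zero growth, the dip alone makes the block contrast significant in 64–95%.

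Volumes, growth, dip and variance are all assumed. The series were generated with a log-linear trend, which favours segmented regression, and autocorrelation was not simulated.

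**Step 5. Direction by measure.**

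- Referral volume: rising demand biases upward.
- Waits: rising demand against fixed capacity lengthens waits, while the Hypothesis section expects them to fall below 30 calendar days. It would tend to mask a benefit. A clearing backlog would mimic one.
- Booking proportion: demand enters numerator and denominator, so the direction is undetermined.

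**The case against.** The strongest reply has five parts.

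- **Calendar time is not ignored.** The plan has two historical windows, compares them with each other and adjusts for COVID period. This is fair and must be acknowledged, but step 3 shows that it does not separate period from program.
- **Referral volume is not tied to the control windows.** This stands. The plan says only before and after for that measure, so the percentages in step 2 assume that the stated windows are used for it. No trend term is stated under either reading.
- **An article condenses a fuller plan.** The model may be set out elsewhere. But the contrast and the causal question are stated here, as are the comparator windows for bookings and waits. The point concerns what is fixed, not a missing detail.
- **Direct booking changes structurally.** The Health economic evaluation section describes non-urgent patients being waitlisted for a clinician as the gateway to psychiatry. Drift of a few percent a year is then a weak rival explanation for a large jump in direct booking. This stands for whether a change occurred; its size still depends on the pre-launch path.
- **Demand may have surged and receded.** The Background gives no local counts. A surge that later fell back would bias against finding a rise in referrals.

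A reader might infer that rising demand is credited to RASP on all three measures. The documents do not support that. It applies to referral volume and to booking counts; for waits it would tend to work the other way, and for the booking proportion the direction is not determined.

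**Conclusion.** The point holds in this form: as stated, the access measures do not separate secular change that predates RASP from a RASP effect, and the planned matching and COVID-period adjustment do not repair it. The bias is upward for referral volume if demand was already rising, may go either way for waits, and is undetermined for the booking proportion.

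The size is unknown. As an illustration that rests on steady 3% yearly growth, a RASP period running from April 2023 for 24 months, and use of the stated windows, referral volume would appear about 9% or 19% higher with no RASP effect, depending on the window. The simulated false-positive rates depend further on assumed volumes and variability, and no magnitude was derived for waits or for the booking proportion. It would go too far to say that the plan disregards calendar time, or that a false positive is likely on the primary access outcomes. What can be said is that a difference on these measures could not be attributed to the program. The plan should be changed.

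**What to change.** In the Study objectives and Outcome measures sections, specify that PHP referrals, direct psychiatry bookings (count and share) and waits to psychiatrist will be analysed as monthly Central Intake series, unbroken from May 2017 through March 2023 and then through the RASP period. Use segmented regression with a pre-launch trend, a COVID term, a step and a slope change at April 2023, and autocorrelation-robust standard errors. State the RASP effect as the departure from the pre-launch trend, and report block differences as descriptive only.

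Keep the existing windows for the patient-level cohort. Leaving out June 2022 to March 2023 can be justified there by the one-year follow-up. The access measures do not need that follow-up, and those months carry the most information on the trend just before launch.

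The cost is extraction of monthly aggregates for the months outside the two windows, a small change of model, and a wider interval than the block comparison gives.
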